## Methods/Design

### Design

A RCT will be conducted for both school-based skills-training programs targeting: 1) skills to deal with performance anxiety and 2) social skills. For each skills-training program, students who have indicated interest in attending a training at their school, will be randomized by the first author (stratified for education level) into the experimental group in which the training starts immediately or into a waitlist control group that receives the training approximately eight weeks later (see Fig. 2), using computerized randomization in a 1:1 ratio. We will use a multi-method (questionnaires and physiological data) and a multi-informant (students, parents and trainers) design and will recruit a mixed-ethnicity sample of students from different educational levels.

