### Study sample

For each school-based skills-training program we aim to include *N* = 130 students to ensure there is enough power for the analyses (*N* = 65 for both the experimental and waitlist control group). A total of *N* = 260 students will be included. This sample size is sufficient to investigate the effectiveness of the interventions and potential moderators, with a power of .80, an alpha of .05 and a medium effect size of .25 [63].

Participants are mixed-ethnicity students in the first, second, and third year of secondary schools (7th, 8th and 9th Grade students) of at least three schools in the Netherlands that offer education at various levels (from vocational education level to preparatory university education level). The students will be between 11 and 16 years old.

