### Interventions

Students in the experimental condition of each skills-training program will participate in seven 45-min small-group sessions during consecutive weeks. Weekly sessions will take place at the school of the students and the sessions will be delivered by an experienced trainer or trained teacher in small groups. The performance anxiety skills-training program consists of cognitive coping strategies (e.g., negative thought restructuring and managing emotions), relaxation techniques and dealing with pressure. The social skills training program consists of social skill building (e.g., identifying personal qualities, giving own opinions, setting boundaries, and standing up for yourself) and cognitive coping strategies (e.g., managing emotions).

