### Statistical analyses

To examine the effectiveness of the skills-training programs, the effects of all outcome measures will be investigated by conducting analyses of covariance (ANCOVAs). The dependent variables are the outcome measures at post-test (program targets, direct program outcomes and mental health outcomes), the independent variables are the conditions and the covariates are the pre-test (baseline) measurements of the outcome measures. The effect of potential categorical and continuous moderators on the effectiveness of the skills-training programs on the specific goals of the programs and mental health of students will be examined by adding the moderators to the ANCOVAs. Data will be imported from an online server software (i.e., Qualtrics) and will be securely stored at the server of Utrecht University where data back-ups will be performed regularly.

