Third, a challenge in this study is to implement the skills-training programs at schools because of logistics (i.e., different locations and scheduling) and the participation and involvement of multiple parties (i.e., researchers, schools, students, parents, youth care organizations that provide the skills-training programs, and municipalities involved). With regard to the latter, multiple schools and multiple organizations offering skills-training programs are involved in this study. To strengthen the collaboration between the schools and the youth care organizations, we will organize regular meetings with all parties involved and aim to match the schools with suitable youth care organizations. With regard to logistics, it is very important that enrollment in the skills-training programs and arrangements in terms of schedules and locations will be timely communicated with the schools and youth care organizations. The researchers will try to overcome potential implementation issues by being present at the schools at least once a week, by giving weekly updates to the youth care organizations, and by being available for consultation at any time during the referral process and skills-training programs.

Fourth, the participating schools do not belong to the same municipality geographically, which complicates the financial conditions for the skills-training programs. To overcome financial issues, we will talk to different municipalities to obtain funding for the skills-training programs. Finally, it is important to be aware that in the Netherlands, school and youth care systems are completely separate, both organizationally as well as financially, which makes cooperation complicated. We try to overcome this challenge by giving regular updates and organize meetings with all parties involved, to promote a fruitful collaboration.

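### The stated ANCOVA treats trained students as independent although only the trained arm is nested in small groups; any correlation the training induces makes standard errors too small

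*Protocol article*

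**What the plan says.** Allocation is of individual students within each program, stratified by education level, "using computerized randomization in a 1:1 ratio" (Design). Students in the experimental arm "will participate in seven 45-min small-group sessions during consecutive weeks", and "the sessions will be delivered by an experienced trainer or trained teacher in small groups" (Interventions). According to the Waitlist-control group section, the control arm gets no training until its post-test is done. At the time of comparison, training groups therefore exist in one arm only.

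The Statistical analyses section names the model. The post-test outcome is the dependent variable, and "the independent variables are the conditions and the covariates are the pre-test (baseline) measurements of the outcome measures". Moderators are added to the same model. Nothing in it refers to training group or trainer.

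The Study sample section sets 130 students per program, 65 per arm, "with a power of .80, an alpha of .05 and a medium effect size of .25". It mentions no ICC, group size or design effect.

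The Background section expects a stronger bond between participant and trainer to improve the outcome. It also lists program integrity and trainer characteristics as possible moderators.

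**The concern.** Ordinary ANCOVA assumes that, given condition and baseline, students' residuals are independent. Seven weekly sessions with the same peers and leader can push the members of a group in the same direction. If so, 65 trained students carry less information than 65 independent ones, and the model does not see it. P-values and confidence intervals are then too optimistic, and variation between groups or trainers can be read as a program effect. The same model is planned for all outcomes of both trials.

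The protocol's own reasoning points to some correlation. If alliance and delivery affect outcome, and both differ between trainers, students who share a trainer will have correlated outcomes.

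**Working it through.** **1. The plan's own sample size.** Inputs from Study sample: alpha .05 (taken as two-sided), power .80, effect size .25, 65 per arm. Reading .25 as Cohen's f (d = 0.5 for two groups), the noncentral F-test for independent students needs 128 in total (power .801), and 130 gives power .808. Reading .25 as d would need 252 per arm, so f is the reading that fits. The stated 130 is reproduced, but only for independent students.

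**2. Variance with groups in one arm.** Let m be the group size and ICC the correlation that training induces within a group after baseline adjustment. The design effect in the trained arm is DE = 1 + (m − 1) × ICC; in the waitlist arm it is 1. With equal arms, the true variance of the effect divided by the ANCOVA variance is

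F = (DE + 1)/2 = 1 + (m − 1) × ICC/2.

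The actual two-sided type I error is 2 × [1 − Φ(1.96/√F)].

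Example, m = 8 and ICC .10: F = 1 + 7 × .10/2 = 1.35; 1.96/√1.35 = 1.687; type I error 9.2%. At ICC .05 and .15, F is 1.18 and 1.53, giving 7.1% and about 11.3%.

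**3. Range.** Neither m nor ICC is in the document, so both are assumptions. The type I errors below come from simulation (40,000 runs per setting, 65 per arm, baseline-adjusted residuals, leftover students spread over the groups). Power is for d = 0.5 with the correct variance: Φ(0.5/√[(DE + 1)/65] − 1.96), with DE weighted for unequal group sizes.

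| Group size | Groups | Type I, ICC .01 | Type I, ICC .05 | Type I, ICC .10 | Power, ICC .05 | Power, ICC .10 |
|---|---|---|---|---|---|---|
| 5 | 13 | 5.1% | 6.1% | 7.2% | .776 | .740 |
| 6 | 10 | 5.3% | 6.7% | 8.3% | .762 | .713 |
| 8 | 8 | 5.5% | 7.6% | 9.2% | .747 | .687 |
| 10 | 6 | 5.6% | 7.9% | 11.0% | .724 | .646 |

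With ICC 0, the same power formula gives .813. The true standard error is about 5% (m = 5, ICC .05) to 22% (m = 10, ICC .10) larger than the ANCOVA reports. Over that span, 80% power would need about 70 to 94 students per arm.

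**4. Shared trainers.** The document does not say whether one trainer leads several groups. If so, the clusters are larger: assuming four trainers with about 16 students each and ICC .05, the type I error is about 9.5%.

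**5. Similarity that existed before allocation.** A separate simulation used 8 pre-existing clusters of 16 students with ICC .10, individual randomisation, no training effect and an unadjusted test. It rejected in about 4.9% of runs under simple randomisation and 3.9% when arms were balanced within cluster. This kind of similarity does not inflate the error.

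**The case against.** **The size is assumed.** The document says only that groups are small. With groups of 4 or 5 and ICC .02, the formula gives 5.4–5.5%. This stands: a reader might infer that the error is certain to be seriously inflated, and the document does not support that. It supports the direction for any positive induced correlation, and a range for the size.

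**Schools as the source.** A reader might infer from the Discussion's remark that "multiple schools and multiple organizations offering skills-training programs are involved in this study" that clustering by school inflates the error. It does not. Students are randomised individually, so school similarity is present in both arms, and ignoring it leaves the test correct or slightly conservative (step 5). Only correlation created by the training itself counts.

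**No effect, no group effects.** If training changed no student's outcome, randomisation would protect the test. That is true, but the null of interest is a zero average effect, and groups or trainers can vary around a zero average. When the average is not zero, confidence intervals are still too narrow for conclusions beyond these particular groups.

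**Not every outcome is hit equally.** Physiology is measured in about 40 students per program. Assuming 20 of them are trained and spread over 8 groups, about 2.5 per group, the formula gives 5.4% at ICC .05. This stands.

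**Detail for the analysis plan.** Degrees of freedom and error structure are often left to an analysis plan. But this section does not leave the model open: it names the method, the independent variable and the covariates.

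**Conclusion.** The stated model does not fit the stated design, and the point should be corrected before analysis. The conclusion is conditional: if training induces any positive within-group correlation, the ANCOVA standard errors are too small and the type I error is above the nominal 5%. It returns to 5% only if that correlation is zero, which sits badly with the protocol's own expectations about trainer alliance. For assumed groups of 5 to 10, the excess runs from negligible (ICC .01) to roughly double the nominal rate (ICC .10, the larger groups). The power claim of .80 at 130 students holds for independent students only.

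**What to change.** **Statistical analyses.** Replace the plain ANCOVA by a partially nested mixed model: post-test outcome on condition and baseline value, with a random intercept for training group in the trained arm only (waitlist students as singletons) and Satterthwaite or Kenward-Roger degrees of freedom. Link each trained student to a group and trainer identifier. The trainer-level moderators already require a link from student to trainer, so this adds little work.

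**Study sample.** State that power .80 at 130 per program assumes independent students, and give the power under an assumed ICC and group size, using the range above or one the sponsor can justify.

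**Cost.** Wider confidence intervals and a less favourable stated power. The group variance will also be estimated imprecisely, since the assumed sizes give only 6 to 13 groups per program, and it may be estimated as zero. Changing the model does not recover the lost power; only more students would.

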Additionally, program characteristics, i.e., treatment alliance, program integrity and trainer characteristics such as ethnicity, experience and perceived competence, may moderate the effectiveness of the skills-training programs. Treatment alliance is the perceived bond between the participant of the skills-training program and the group leader (i.e., trainer), which is demonstrated to be positively associated with treatment outcome in depressive patients [53] and in children and adolescents with anxiety disorders [59, 60]. Hence, it is expected that high participant-trainer alliance contributes to a more beneficial outcome. Program integrity refers to the extent to which a program is implemented as originally planned, and is reported by very few studies [61]. Finding non-significant effects may not be caused by an ineffective program, but because a program is not carried out as intended [62]. Therefore, it is important to examine program integrity in order to correctly draw conclusions on the effectiveness of the skills-training programs.

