### Waitlist-control group

The waitlist group will not receive any training during the implementation of the intervention in the experimental group and will only complete the pre-and post-intervention measurements. The waitlist group will receive the intervention immediately after the post-intervention measurements, approximately 8 weeks later than the experimental group.

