S*tressful life events* will be measured with the Negative Life Events Inventory [89, 90], translated into Dutch. This instrument is a 20-item checklist of negative life events (e.g., “Somebody in my family had a serious illness”). Students are asked to indicate whether an event had occurred during the previous year and includes events that occurred to family members and directly to themselves. The internal consistency is between .67 and .71 [89, 90]. Students will complete this instrument after completion of the skills-training program (post-intervention measurement).

*Perceived parental pressure* will be measured with the subscale parental pressure of the Multidimensional Inventory of Perfectionism in Sport (MIPS) [91], translated into Dutch. The perceived parental pressure subscale consists of 8 items (e.g., “My parents set extremely high standards for me”). The internal consistency is good (above .92) [91, 92]. Parental pressure has a high temporal stability [93] and students will therefore complete this instrument at post-measurement.

*Treatment alliance* will be measured with the Therapy Alliance Scale for Children (TASC) [94], translated into Dutch and altered for use in group skills-training programs. This is a 12-item instrument measuring the bond-aspect of alliance (6 items, e.g., “I like my trainer”) and the tasks of the program (6 items, e.g., “I work with my trainer on solving my problems”). This instrument has good internal consistency (above .70) [95, 96] and is completed by students after completion of the skills-training program (post-intervention measurement).

*Program integrity* will be measured with a questionnaire specifically developed for this study. After each session, trainers will be asked to evaluate the session by registering if they carried out the session as intended (e.g., is the content of the session sufficiently treated, are other components discussed, and what was their overall impression of the session).

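### Treatment alliance and programme integrity have no value in the waitlist arm at T2, so the stated ANCOVA cannot test them as moderators; trainer characteristics need a stated link to waitlist students

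*Protocol article*

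**What the plan says.** The second aim (Background) is to study moderators of both programmes' effectiveness, including programme characteristics. The Background states that "treatment alliance, program integrity and trainer characteristics such as ethnicity, experience and perceived competence, may moderate the effectiveness of the skills-training programs". Table 1 gives alliance, integrity and trainers' experience and competence the variable type of moderator.

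Statistical analyses describes one model, an ANCOVA of the post-test score on condition with the baseline score as covariate. Moderators of every kind "will be examined by adding the moderators to the ANCOVAs". No separate method is given for programme characteristics.

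Three other places determine what data exist at T2:

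- Waitlist-control group: "The waitlist group will not receive any training during the implementation of the intervention in the experimental group". This arm completes only the two assessments and is trained after the second.
- Moderators, on the alliance scale: it "is completed by students after completion of the skills-training program (post-intervention measurement"), and its items concern the trainer and the tasks of the programme. Integrity is recorded by trainers after each session.
- Data collection and Table 1: trainer characteristics are collected before the interventions start.

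Study sample plans 65 students "for both the experimental and waitlist control group" of each programme. The Discussion says the sample is large enough to examine moderators and lists programme characteristics among them.

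**The concern.** A moderator of a randomised effect is a variable across whose levels the difference between arms varies. To estimate that, both arms must have a value of the variable. By design, alliance and integrity come into being only through the training, and the waitlist arm has had none when the outcome is measured.

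If the plan is followed literally, the model either loses its control arm or returns an association among trained students only. Labelled as moderation, that association would suggest that the programme works better where alliance or integrity is higher. For alliance it could equally mean that students who improved came to like their trainer more, or that some students rate everything favourably. Alliance is reported by the same student at the same assessment as the self-reported outcomes. That part of the second aim would then rest on a non-randomised comparison presented under the heading of a randomised trial.

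**Working it through.** **1. The plan's own sample size.** Inputs from Study sample and Design: 130 per programme, 65 per arm, "using computerized randomization in a 1:1 ratio", "with a power of .80, an alpha of .05 and a medium effect size of .25". I read .25 as Cohen's f and assume a 1-df F-test. The noncentrality is λ = f²N.

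- N = 128 is the smallest total that gives power of at least .80.
- At N = 130: λ = 0.0625 × 130 = 8.125. With one covariate the error df are 130 − 3 = 127, and power is 0.81.

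The stated 130 therefore reproduces. The problem lies in what can be identified, not in this calculation.

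**2. Can the interaction be estimated?** Let g = 1 for trained and 0 for waitlist, and let M be the moderator. The moderation model has five columns: intercept, baseline, g, M and g·M.

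| Situation | Rows | Rank (of 5) | Consequence |
|---|---|---|---|
| M observed in both arms | 130 | 5 | Interaction estimable |
| M missing in waitlist, complete cases | 65 | 3 | g equals the intercept and g·M equals M; neither the condition effect nor the interaction is estimable |
| M set to a constant c in waitlist | 130 | 4 | M and g·M cannot be separated |

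The last row follows for any c, because M = c − c·g + g·M holds for every student. With c = 0 this is M = g·M. All 130 students and a condition coefficient remain, but the single coefficient left for M is its slope among trained students.

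**3. Is that slope effect modification?** A simulation under assumed values shows that it need not be. For 65 trained students, a trait U raises both alliance and the T2 score:

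- alliance = 0.5·U + √0.75·e₁
- T2 = 0.5·baseline + 0.5·U + 0.5 + 0.7·e₂

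U, baseline, e₁ and e₂ are independent standard normal. Training adds the same 0.5 for everyone, so there is no moderation. The expected slope of T2 on alliance is 0.5 × 0.5 = 0.25, because alliance has variance 0.25 + 0.75 = 1. Over 4,000 runs the mean slope was 0.25, and it was significant at 5% in 67% of runs. The percentage depends on the assumed coefficients. What it shows is that such a slope can arise with no moderation at all.

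**4. Power within the trained arm.** Apply the same F-test to the baseline-adjusted slope of M, carrying f = .25 over as an assumption. At n = 65, λ = 0.0625 × 65 = 4.0625 and the error df are 65 − 3 = 62.

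- Power is 0.51.
- The smallest effect with 80% power is f = 0.35, which is a partial r of 0.353/√(1 + 0.353²) = 0.33.
- For f = .25, 128 trained students would be needed.
- If fewer T2 forms are completed (assumed), power is 0.48 at n = 60, 0.44 at n = 55 and 0.41 at n = 50.

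These figures treat students as independent. Dependence within training groups would lower them.

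**The case against.** **The article is condensed, and model detail belongs in an analysis plan that is not shown.** This would answer a complaint about missing detail. Here, however, the article itself fixes one method for all moderators and names alliance and integrity among them. An analysis plan that follows it inherits the problem, and one that departs from it contradicts the article.

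**The waitlist arm is trained later, so values will eventually exist.** Alliance or integrity arising after T2 cannot modify a contrast measured at T2, and no later assessment of that arm is described.

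**Trainer characteristics are measured at T1.** This stands. A reader might infer that no programme characteristic can ever be tested as a moderator, but the documents do not support that. Waitlisted students later receive the same training, so each could be assigned the characteristics of a planned trainer. The text states no such link, but it does not exclude one.

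**Within-arm associations have their own use.** This also stands. The Background expects high alliance to go with better outcomes, and wants integrity partly to help interpret null findings. Neither purpose needs an interaction. For these variables the fault is the moderator label and the model assigned to them, not the decision to collect them.

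**Conclusion.** For treatment alliance and programme integrity, moderation of the randomised effect is not identifiable under this design, and the stated analysis cannot answer that part of the second aim. This follows from the timing and exposure rules alone and needs no numerical assumption. For trainer characteristics it is identifiable only if a link from waitlisted students to a planned trainer is pre-specified.

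The power of 0.51 rests on reading .25 as Cohen's f, applying the same f to a slope, 65 complete trained students and no clustering.

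Three stronger readings are tempting but not supported:

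- That adding a moderator means fitting its main effect only. The same sentence gives the target as the moderators' effect on effectiveness, so the wording is fair shorthand for including the interaction.
- That the effective sample for integrity or trainer variables equals the number of training groups. That would need an intraclass correlation of 1. The article says only that groups are small, so no group count can be derived.
- That the trial's main comparison is damaged. The effectiveness ANCOVAs, and student and parent moderators observed in both arms, are untouched by this point.

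This should be fixed, but it does not threaten the main result.

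**What to change.** 1. Take alliance and integrity out of the moderator ANCOVAs and change their variable type in Table 1.
2. Analyse them within the trained arm as predictors of the T2 outcome, adjusted for the T1 score and allowing for training group. Report them as non-randomised process associations.
3. For trainer characteristics, either pre-specify how each waitlisted student is linked to a planned trainer, and test the condition-by-moderator term on that basis, or treat them as in step 2.
4. Qualify the Discussion's statement on sample size: for programme characteristics analysed within the trained arm, n is 65 per programme and power at f = .25 is about 0.51 before clustering.

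The cost is rewording the moderator list, Table 1, the analysis paragraph and one sentence of the Discussion. Choosing the trainer link also means recording the planned trainer for each waitlisted student. No further outcome data are needed. The price is a weaker claim for programme characteristics.
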